### Candidate predictors

Candidate predictors are the variables that predict the prognostic outcome. These can include patient demographics, clinical history, physical examination, disease characteristics, test results and treatments used.

When choosing the potential candidate predictors, various recommendations have been made:Predictors already reported as prognostic should be included.^61 62^
The selection should be informed by clinical understanding (ie, expert opinion) to ensure the list is comprehensive and clinically relevant.^45 62^
Where predictors are highly correlated (eg, weight and body mass index), only one should be selected.^62^
Potential confounders (ie, a variable that may be associated with another predictor and the outcome) should be included to permit these to be accounted for during analysis.^63^
Use of predictors that occur infrequently can lead to inaccurate results.^62 64^
Candidate predictors should be:available at the time when the model is intended to be used.^54^
clearly defined, standardised and reproducible (to enhance generalisability and applicability of study results to practice).^54^
have minimal measurement error (as this may dilute their prognostic value).^49^

A review of the published literature identified 59 possible predictors, but substantial variations were found between studies in terms of the strength of evidence for each predictor. This is potentially due to significant differences in study design, and the outcome measure used (namely adverse drug events, adverse drug reactions, prescribing errors and MRPs). Twenty-seven of the potential predictors were selected, based on the strength of published evidence in addition to the criteria stated above, for inclusion in a survey to obtain expert opinion from healthcare professionals and patient/public representatives. The survey was administered during April–June 2016, and a total of 247 responses were received. The results showed that the majority of the potential predictors (23 of 27) were considered ‘important’ or ‘very important’. In addition, a significant number of additional predictors (59) were suggested.^65^

When developing a prognostic model, it is necessary to limit the number of candidate predictors used to prevent ‘overfitting’ or ‘underfitting’. Both can lead to poor performance when the model is used in an independent data set.^55^ One method to reduce the number of candidate predictors is to base the selection on the univariable association between each predictor and the outcome. This is not recommended as it results in overfitting due to selection bias,^61^ and can lead to predictors being wrongly excluded from the model due to the fact that the association may only become significant after adjustment for the other predictors. It is recommended that the candidate predictors are selected a priori.^47 64^ We have therefore chosen to preselect the candidate predictors for development of the MOAT (table 1) using the recommendations above. An additional consideration was the selection of predictors that form part of standard clinical data sets. This was to increase the reliability of the data and minimise the potential for missing data, and to enable the MOAT to be readily incorporated into clinical practice without the need for additional tests/measurements.

**Table 1 T1:** Preselected candidate predictors for the Medicines Optimisation Assessment Tool

Variable	Details/categories	Type of measurement	Number of variables*
**Demographic**			
Age	Age at admission to hospital (in years)	Continuous numeric	1
Socioeconomic status	Based on the English indices of deprivation 2015 (Index of Multiple Deprivation Rank)	Continuous numeric	1
**Patient-related**			
Previous allergy/adverse drug reaction	Yes/No	Binary	1
Body mass index	First documented result following admission	Continuous numeric	1
Number of hospital admissions	Number of admissions to the study hospital in the previous 6 months	Continuous numeric	1
Primary diagnosis	Categorised by ICD-10 coding: Endocrine Nutritional and metabolic diseases Diseases of the circulatory system Diseases of the respiratory system Diseases of the digestive system Diseases of the genitourinary system Other (all other diagnoses combined)	Nominal categorical	6
Number of comorbidities	From hospital clinical coding data (ICD-10 codes)	Continuous numeric	1
History of dementia	From hospital clinical coding data (ICD-10 codes)	Binary	1
**Medicines-related**			
Number of medicines prescribed	Number of ‘regular’ medicines prescribed on the first full day of admission to hospital (ie, excluding ‘when required’ and ‘once only’ medicines, dietary products, non-medicated topical products (eg, emollients), wound dressings)	Continuous numeric	1
Use of ‘high risk medicines’	Prescribed as a ‘regular’ medicine during the hospital admission: Anticoagulants/direct oral anticoagulants Therapeutic heparin Antidiabetic medication Opiates (excluding codeine, tramadol and dihydrocodeine) Aminoglycosides and glycopeptides Antibiotics (excluding aminoglycosides and glycopeptides) Theophylline and aminophylline Epilepsy medicines Antipsychotics Immunosuppressants (excluding corticosteroids) Cytotoxics Lithium Antiarrhythmics Antidepressants Other (clozapine, antiretrovirals, medicines for Parkinson’s disease)	Binary (for each group)	15
Parenteral administration route	Administration of one or more regular medicines via the parenteral route (intravenous, intramuscular, subcutaneous) during the hospital admission (excluding prophylactic low molecular weight heparins, fluid replacement therapy)	Binary	1

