MRP data will be collected for all study patients from admission to discharge from hospital, or the date the study closes (2 weeks after inclusion of the final study patient), whichever occurs sooner. A study close date will be used to facilitate practicality in terms of data collection, while permitting data to be collected from admission to discharge for the majority of study patients (as the mean length of stay at the study sites is approximately 6 days).

Previous research into the detection of prescribing errors, a subset of MRPs, has shown that the observed incidence is extremely dependent on the method of detection.^53^ We have chosen to use prospective identification by pharmacists for this study because (1) the purpose of the study is to develop a prognostic model for MRPs that can be identified during routine clinical practice by pharmacists; (2) it will permit the identification/inclusion of MRPs that are not routinely recorded in medical notes, such as potential prescribing or administration errors that are intercepted; and (3) it will permit the MRPs to be identified by staff personally involved in the care of the study patients, increasing clinical and practical relevance.

It is acknowledged that a limitation will be the possibility of incomplete data due to pharmacy staff being required to complete this work in addition to other routine duties. To minimise this, the principal investigator will work closely with the study sites to ensure that data collection occurs at an optimal time in terms of staffing levels and workload. Staff involved in MRP data collection will also be provided with initial training to improve the consistency and reliability of data collection. The principal investigator will review all data collection forms daily and seek clarification where needed, and provide the pharmacists with ongoing fidelity training.

We also recognise that identification of MRPs may vary depending on the knowledge, experience and skills of the pharmacists collecting data. To quantify this potential variability, a simulated ‘MRP identification assessment exercise’ will be developed and used in a training scenario. Each simulated MRP will be treated as having a binary outcome in terms of whether or not it is identified by each pharmacist. Fleiss’ kappa will be used to calculate the level of agreement between pharmacists.

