In prognostic research it is recommended that data on candidate predictors is collected blind, in terms of knowledge of the outcome and other predictors.^49 55^ This is particularly important when subjective judgement is required as it prevents the assessment being influenced, which could artificially increase the associations between the predictors and outcomes. Full blinding will not be possible for this study as the independent data analysts and the principal investigator will not be blinded to all other predictor data, and the principal investigator will not be blinded to the MRP status. It is anticipated that this will have minimal impact on the accuracy of data collection as all candidate predictors selected for this study are objective measurements that are independent of observer interpretation; therefore, subjective judgement is not required. In addition all candidate predictors will be recorded contemporaneously during the admission as part of routine care/documentation, therefore without knowledge of the MRP status. To identify any possible bias, the principal investigator will perform a double check on data entry. This will involve a double check on a randomly selected 10% sample of the 1500 study patients. Sixteen data items will be checked for each of these 150 patients, giving a total of 2400 data items. The accuracy will be calculated as the percentage of data items recorded correctly. Data entry will be refined if necessary.

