#### Model building

We will use multivariable logistic regression modelling to develop the MOAT. This has been chosen as the outcome is binary, and all participants will be followed up to the end of the study period. The aim is to produce a parsimonious model to increase clinical applicability while retaining reasonable predictive performance.

Backwards elimination will be used to reduce the set of candidate predictors. The Akaike Information Criterion (AIC) will be used to exclude predictors. We chose to use the AIC due to the relatively small data set (hence relatively larger p values for the predictors), as it is less likely to result in underfitting than alternative methods.^69^

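### Sixteen of the 37 candidate variables are scored over the whole admission, the same window as the outcome, so they can follow the MRP and track length of stay

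*Protocol article*

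**What the plan says.** Under Candidate predictors, the protocol article lists properties that a predictor should have. One is that it be "available at the time when the model is intended to be used".

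Table 1 then sets the time at which each predictor is read:

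- **High-risk medicines (15 binary variables):** "Prescribed as a ‘regular’ medicine during the hospital admission".
- **Parenteral route (1 binary variable):** "Administration of one or more regular medicines via the parenteral route (intravenous, intramuscular, subcutaneous) during the hospital admission".
- **Number of medicines:** regular medicines on the first full day of the admission.
- **Laboratory values and BMI:** the first result documented after admission.
- **Number of comorbidities, dementia, primary diagnosis and part of liver disease:** ICD-10 coding, with no time window stated.

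On the outcome, the Outcome section says that "MRP data will be collected for all study patients from admission to discharge from hospital, or the date the study closes", whichever comes first. Model building justifies logistic regression partly on the ground that "all participants will be followed up to the end of the study period".

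All predictors are collected retrospectively. Optimism is to be handled by bootstrap validation and a shrinkage factor.

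**The concern.** A prognostic model uses what is known at a given moment to predict what happens later. For the 16 medicines variables the predictor and outcome windows coincide, and nothing requires the exposure to come first. Two mechanisms follow.

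1. **Shared exposure time.** A longer stay gives more opportunity both to start a medicine or a parenteral route and to have an MRP recorded. The two become associated even if the medicine carries no risk.
2. **Reverse causation.** The MRP definition covers anything that interferes with an optimal outcome. If a pharmacist finds that a regular medicine was omitted and it is then prescribed, the predictor turns positive because of the outcome.

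The coefficients, and the score points derived from them, would then mix prognosis with length of stay and with the pharmacist's own interventions. The AUC, calibration, sensitivity and specificity would be computed on the same variables, so the study would not reveal the problem. It would appear when the tool is applied to patients whose later prescriptions are not yet known.

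**Working it through.** **Reproducing the plan's figures.** Events: 1500 × 0.32 = 480. The Table 1 counts sum to 37. Events per variable (EPV): 480 / 37 = 12.97, stated as 13. All agree, and none is in dispute.

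**Share of variables affected.** 15 + 1 = 16 of 37, or 43%.

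**Comparing the windows.** Medicine count: first full day. Laboratory values and BMI: first result. The 16 variables: whole admission. Outcome: admission to discharge or study close. Only the 16 are explicitly given the outcome's window. A whole-admission *no* is known only at discharge, so these variables do not meet the availability rule.

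**Size of the shared-time effect for a medicine with no true effect.**

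From the documents: mean stay 6 days, prevalence 32%. Assumed, because the documents give no figures: stay is gamma with shape *k*; a fraction *p* is exposed at baseline; later starts occur at rate *h* per day; MRPs arise at a constant rate λ, independently of exposure.

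Write G(r) = (1 + 6r/k)^(−k), the chance that an event with daily rate r does not occur during the stay.

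- λ solves G(λ) = 0.68.
- P(never exposed) = (1 − p)·G(h).
- P(never exposed, no MRP) = (1 − p)·G(λ + h).

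The other cells follow by subtraction.

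Middle case, k = 2, p = 0.20, h = 0.05:

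- (1 + 3λ)^(−2) = 0.68, so λ = 0.0709.
- P(never exposed) = 0.80 × 1.15^(−2) = 0.6049.
- P(never exposed, no MRP) = 0.80 × (1 + 3 × 0.1209)^(−2) = 0.4308.
- P(never exposed, MRP) = 0.6049 − 0.4308 = 0.1741.
- P(exposed, no MRP) = 0.68 − 0.4308 = 0.2492.
- P(exposed, MRP) = 0.32 − 0.1741 = 0.1459.
- Odds ratio = (0.1459 × 0.4308) / (0.2492 × 0.1741) = 1.45.
- Single-predictor AUC = 0.5 + 0.5 × (0.1459/0.32 − 0.2492/0.68) = 0.545.

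Simulation with 2 million patients per setting gave the same 1.45 and 0.545. In it, 29% of exposed patients with an MRP were first exposed after that MRP. The same variable scored at baseline gave 1.00.

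| Assumptions | Spurious odds ratio |
|---|---|
| p = 0.10, h = 0.01 to 0.03, k = 1 or 2, MRPs spread evenly | 1.23 to 1.90 |
| Same, half of MRPs at admission | 1.13 to 1.46 |
| Same, three quarters of MRPs at admission | 1.07 to 1.24 |
| p = 0.10 to 0.30, h = 0.02 to 0.10, k = 1, 2 or 4, MRPs spread evenly | 1.09 to 2.66 |
| p = 0.10, h = 0.001, k = 1 or 2, MRPs spread evenly | 1.03 to 1.06 |
| Scored at baseline | 0.99 to 1.01 |

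In the fourth row the single-predictor AUC was 0.51 to 0.62, and 13% to 41% of exposed patients with an MRP were first exposed after it. No row includes reverse causation.

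**Whether a planned step removes it.** Bootstrapping estimates the loss from overfitting. Each resample carries the same predictor definitions and the same overlap, so neither the optimism estimate nor the shrinkage factor sees it.

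**Follow-up.** Under the Outcome section, follow-up ends at discharge or study close and so varies between patients. The Model building sentence says otherwise.

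**The case against.** The best defence is that the protocol never says the tool is used once, at admission. It speaks of use in hospital and foresees automated real-time assessment later. If patients were rescored, a medicine started on day 3 would be known on day 3. That part stands, and a reader who infers that admission is the only intended time of use goes beyond the text. It does not rescue the definition. A model fitted to ever-versus-never use over the stay does not estimate risk given use so far, and *never* is known only at discharge.

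The size is also uncertain. Start rates and MRP timing are assumed. Groups such as lithium or epilepsy medicines may rarely be started in hospital, and if most MRPs arise at admission the odds ratios shrink to 1.07 to 1.24. This stands as a limit on magnitude.

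A reader might also take the statement that "all candidate predictors will be recorded contemporaneously during the admission as part of routine care/documentation, therefore without knowledge of the MRP status" to be false. It sits in a discussion of blinding and addresses observer bias. It neither claims nor secures that exposure precedes outcome, so it is no error, but it is no answer either.

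Finally, external validation is required before routine use and the analysis plan may be modified. Both are true, but validation with the same definitions would repeat the overlap.

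**Conclusion.** The point holds for the 16 medicines variables. Their window matches that of the outcome, against the protocol's own availability rule and its handling of the medicine count, laboratory values and BMI. No later planned step repairs this.

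In every null scenario with starts after admission, the bias was upward. Its size rests on the assumed stay distribution, baseline use, start rates and MRP timing: roughly 1.07 to 1.9 in the main set, up to 2.66 under wider assumptions, and close to 1 for medicines seldom started in hospital. Reverse causation is not quantified.

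Two stronger readings are not supported. The coded predictors cannot be said to be read over the whole admission: no window is stated, and in-hospital onset is an inference, weak for a condition such as dementia. The mismatch over follow-up is a wording conflict to correct, and the documents do not show that it alters results materially.

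**What to change.** - State one prediction time.
- Score the 15 high-risk-medicine groups and parenteral route as prescribed or administered by that time. The first full day, or discharge if sooner, would match the medicine count.
- Add an analysis restricted to MRPs identified after that time. Anchoring alone still leaves MRPs found and corrected on day 1 able to turn a predictor positive.
- For ICD-10-coded items, state that the condition must be present at admission.
- Correct the Model building sentence so that it agrees with the Outcome section: discharge or study close, whichever is sooner.

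**Cost.** The changes are mainly to wording and extraction rules. Predictors are read retrospectively from the same prescribing records that supply the first-full-day count, so no new source is needed for the 16 variables. The main analysis keeps 480 expected events, 37 variables and 13 EPV.

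Medicines started later no longer count. The restricted analysis has fewer events and needs the date on which each MRP was identified. If it refits all 37 variables, 10 EPV requires 37 × 10 = 370 events, so it stays at that level only if no more than 480 − 370 = 110 events fall before the prediction time.

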**Laboratory results**			
Renal function	Creatinine clearance calculated using the Cockcroft-Gault equation (using first documented results following admission)	Continuous numeric	1
Liver disease	Liver disease defined as ALT/ALP and/or bilirubin ≥3 times normal range and/or documented liver disease Laboratory results will be the first documented results following admission Documented liver disease will be established from hospital clinical coding data (ICD-10 codes)	Binary	1
Serum albumin	First documented result following admission	Continuous numeric	1
Serum potassium	First documented result following admission	Continuous numeric	1
Serum sodium	First documented result following admission	Continuous numeric	1
White cell count	First documented result following admission	Continuous numeric	1
Platelet count	First documented result following admission	Continuous numeric	1
**Total number of variables***			37

*Number of variables in relation to calculating the ‘events per variable’.

ALP, alkaline phosphatase; ALT, alanine aminotransferase; ICD, International Statistical Classification of Disease and Related Problems.

All data on the candidate predictors will be collected retrospectively. Data will be obtained from the information department at the study hospitals where possible, including demographic, diagnostic and comorbidity data. Laboratory data will be extracted manually from the electronic reporting system used at both hospitals. The remaining data will be extracted manually from patient medical records. Hospital A has electronic medical and prescribing records; Hospital B has paper-based systems. Manual data extraction of laboratory data will be performed by a single data analyst at each study site, independently of the research team. Data from the patient medical records will be collected by the independent data analyst at Hospital A, but due to the use of paper-based systems at Hospital B and the need to read handwritten prescriptions, these data will be extracted by the principal investigator at Hospital B. All manually extracted data will be entered directly into an electronic database. All data will be recorded as reported, with no categorisation of continuous data.

In prognostic research it is recommended that data on candidate predictors is collected blind, in terms of knowledge of the outcome and other predictors.^49 55^ This is particularly important when subjective judgement is required as it prevents the assessment being influenced, which could artificially increase the associations between the predictors and outcomes. Full blinding will not be possible for this study as the independent data analysts and the principal investigator will not be blinded to all other predictor data, and the principal investigator will not be blinded to the MRP status. It is anticipated that this will have minimal impact on the accuracy of data collection as all candidate predictors selected for this study are objective measurements that are independent of observer interpretation; therefore, subjective judgement is not required. In addition all candidate predictors will be recorded contemporaneously during the admission as part of routine care/documentation, therefore without knowledge of the MRP status. To identify any possible bias, the principal investigator will perform a double check on data entry. This will involve a double check on a randomly selected 10% sample of the 1500 study patients. Sixteen data items will be checked for each of these 150 patients, giving a total of 2400 data items. The accuracy will be calculated as the percentage of data items recorded correctly. Data entry will be refined if necessary.

#### Sample size calculation

Sample size is often calculated based on significance testing (power calculations), but this is not straightforward for prognostic modelling studies as there is often not a clear ‘measure of effect’ to power the research. An alternative method is to calculate the sample size based on the desired precision of a sample estimate.^55^ An alternative approach that is commonly used is the ‘rule of thumb’ of '10 events per variable’ (EPV).^66^ This method requires the sample size to be based on the prevalence of the outcome measure and the number of candidate predictors that will be used in model development.^49 54 55 66^ Although there is debate over the optimal number of EPV, with recognition that ‘the rule of 10 or more EPV is not a well-defined bright line’,^64^ there is agreement that models developed with less than 10 EPV need to be interpreted with caution.^55 64^ The reason for the potential problem with using less than 10 EPV relates to the reliability of the model when used in a new group of patients. If a model is too closely adapted to the developmental data, it can reflect associations between the candidate predictors and outcome which are due to chance rather than true associations, known as ‘overfitting’ or ‘optimism’.^49 55 61^

For this study the sample size has been dictated by practical considerations (funding, time available and accessibility of data at the study sites), resulting in the capacity to include 1500 (1000 from Hospital A and 500 from Hospital B), plus an additional 10% per site to allow for exclusion of patients who do not meet the eligibility criteria. We have therefore used both the precision and EPV methods to consider the adequacy of this sample size, based on an estimation of the outcome prevalence in the study population.

The outcome of interest for this study is moderate or severe, preventable MRPs in hospitalised UK patients. No estimate for the prevalence of this outcome currently exists, but Blix *et al*
51 (Norway 2004) reported that 81% of 827 hospitalised patients experienced an MRP, with approximately half of all MRPs classified as ‘extremely important’ or ‘major’ in terms of clinical significance (preventability not reported). To establish the prevalence of the outcome in the study population, we carried out pilot work involving 200 patients, and found that 39% (95% CI 32% to 45%) experienced at least one moderate or severe, preventable MRP (using the proposed visual analogue scale for medication errors and a severity score of 3 or more). Although this is consistent with Blix’s work, we recognise that our estimate is based on a small sample of patients (200). In addition the MRPs were severity rated by three members of the expert panel rather than the four proposed for the main study. We have therefore chosen to use the lower CI limit as an estimate of the outcome prevalence, that is, 32%. Given an anticipated outcome prevalence of 32% and a sample of 1500 patients, we anticipate identifying 480 patients with at least one moderate or severe preventable MRP.

To consider the adequacy of the sample size using the precision method, we first established acceptable target sensitivity for the MOAT by including a question in our survey of healthcare professionals and patient/public representatives, detailed above. We proposed a target sensitivity of 90% and asked survey respondents if this was acceptable. This sensitivity was selected based on previous research to develop a ‘clinical decision rule’ to identify emergency department patients at risk of adverse drug events.^67^ Hohl *et al*
67 used a target sensitivity of 90% as this was deemed acceptable by emergency physicians and considered feasible for implementation in terms of workload for pharmacists. A total of 237 responses were received for this question: 189 (80%) answered that 90% was an acceptable target, 21 (9%) answered no and 27 (11%) were ‘unsure’. As a result we concluded that 90% is an acceptable target for sensitivity. Given the anticipated number of study outcomes and a target sensitivity of 90%, this will permit the precision of the sensitivity to be estimated with 95% CIs of ±3%, which we consider to be an acceptable level of precision in terms of clinical usefulness of the MOAT.

For the EPV method our aim would be to have at least 10 events for every variable used in model development. Given the estimate of 480 outcome events, that is to say patients with at least one moderate or severe preventable MRP, this would permit the inclusion of 48 ‘variables’ in model development. The number of variables includes all proposed candidate predictors, interactions examined (ie, where a candidate predictor has a different association with the response depending on the value of a third variable), transformations for continuous predictors (which permits modelling of non-linear predictors) and indicator variables for categorical predictors. We do not hypothesise any interactions a priori. We will explore any potential interactions during the analytical stage to establish whether there are associations that may lead to a better understanding of the final model, but recognise the risk of overfitting caused when numerous interactions are examined, with only the strongest included in the model.^55^ Similarly, we will not know whether transformations are required until we examine the linearity of the continuous predictors.

Table 1 shows the total number of variables that will be used for each candidate predictor (including the indicator variables, which are the artificial variables used to represent distinct groups within a categorical variable). We propose using 37 variables to develop the MOAT, resulting in 13 EPV, given that no interactions or transformations are required.

